#### Inclusion criteria

Adults (> 18 years) with incurred traumatic or non-traumatic SCI between 1 January 2004 and 1 January 2014, and who give their consent to participate.

#### Exclusion criteria

Persons with no SCI:Persons who are unable to give their consent due to cognitive problemsPersons who do not have a permanent/known Norwegian addressAge < 18 years

### Study 2

In study 2, persons with SCIs and ongoing PUs will be assessed for eligibility in a RCT. Eligible persons will be provided with detailed written and verbal information about the project, and asked to sign informed consent before inclusion. The Informed Consent Form is approved by the National Regional Ethical Committee [17]. Relatives and the local caregivers will also be informed and invited to cooperate in the follow-up study. Once the consent is given, baseline data will be collected, randomization will be done and the group allocation will be informed to the participants, either face to face during the outpatient consultation at the SCI departments, or by telephone if the participant is at home.

#### Inclusion criteria

Traumatic or non-traumatic SCIOngoing PUAge > 18 yearsConsent to participate given

#### Exclusion criteria

No SCINo PUAge < 18 yearsNot living in NorwayNo known Norwegian addressParticipants who are unable to give their consent due to cognitive problems

### Randomization and allocation concealment

Participants in the RCT will be randomized directly after baseline assessment to group 1 (the teleSCI group) or to group 2 (the usual care group). The randomization will be stratified with respect to the hospitals, blocked with varying sizes, and carried out by use of the random-number generator in the statistical software SPSS. The randomization sequence list will be created in advance of recruitment, by an experienced scientist who is not a member of the research team. The randomization numbers will be provided in closed and sealed envelopes, unavailable to those who enroll the participants. At least two persons, either investigators or other medical staff members, will be present to secure the allocation procedure. If the participant is included in the teleSCI group, further arrangements for the installation of the telerehabilitation software and training in the use of the software program and equipment will be addressed to the participant, the relatives, and the local caregivers.

### Blinding

In study 1, the participants will be assigned a serial number identification within each SCI unit. This serial number will be used in the analyzing of the questionnaires. No personal identification will be used. In study 2, it will not be possible to blind the participants. The wound assessment tool [24] and the cost-benefit form will, however, be considered by blinded medical professionals not participating in the research project. Only the randomized number, not the identity of the participants, will be known during the analyzing part of study 2.

### Data collection and storage

Patients are assigned a randomly selected project identification/serial number within each SCI department in Norway. This serial number follows the individual patient through the rest of the project. The serial number and person identification form the key code. The key code and the data set will be stored, locked in different fireproof cabinets, where only the main investigator has access. Data and Telecommunications Authority’s requirements for safe information flow will be followed [25]. Only the main investigator will have access to the final trial data set. This is in line with the ethical approval of the study, given by the National Regional Ethical Committee (NREC) in Norway [17]. The main investigator will terminate the trial in 2019, and the collected results will be terminated in 2024, according to the NREC approval.

### Outcome measures

#### Study 1

Study 1 will highlight the national prevalence of PUs in persons who suffered SCIs between January 2004 and January 2014.The study will also analyze causes and risk factors of developing PUs, according to the answers in the participant questionnaires.

#### Study 2

##### Primary endpoints

Study 2 will focus on the effect of using teleSCI compared with other outpatient approaches in the follow-up of persons with PUs after a SCI, measured in terms of percentage wound size healed, and the time to heal. A systematic evaluation of the ulcer will be done, using the validated Time Infection Moisture Edge (TIME) form [26] and the Photographic Wound Assessment Tool (PWAT) scale [27], where the amount of fibrin and granulation tissue present, percentage of epithelialization of the wound, percentage of moisture present, and the appearance of the wound edges will be described. Time to heal will be measured counting days until healing, or measuring the amount of healing at the end of the 12-month follow-up period. Changes in self-reported health-related quality of life (HRQoL) and the need for assistance will be compared using the 12-item Short Form Health Survey (SF-12v) [28], the Five Dimensions European Quality of Life scale (EQ-5D) [23], and the International Spinal Cord Injury Quality of Life questionnaire (ISCI-QoL) basic data set [29]. The SF-12v [28] measures functional health and well-being from the patient’s point of view. The EQ-5D scale [23] measures mobility, self-care, activities, pain, discomfort, and anxiety/depression. The participants perform a self-rating of their health in a box-scale and on a vertical visual analog scale. In the ISCI-QoL questionnaire [29], the participants will rate their physical and psychological health, using a box-scale. The SF-12v [28], EQ-5D [23], and ISCI-QoL [29] will be used as a quantitative measure of the health outcome that reflects the participant’s own health judgment before and, at the end of, the follow-up period. The Spinal Cord Independence Measure, version III (SCIM III) scale [24] has been designed specifically for persons with SCI and is a comprehensive ability-grading scale, focusing on the ability of performing basic tasks, and the effect the SCI has on the overall medical condition and comfort. SCIM III [24] will be rated at baseline and at the end of the follow-up period, and the results from both groups in the RCT will be compared with focus on changes in performing ability during the follow-up period.

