**Method/design:**

The first part of this research project aims to investigate the prevalence of PU among persons with SCI based on an epidemiological design. The study will identify possible risk factors for acquiring PU. A questionnaire focusing on previous and present PUs will be sent to persons who suffered SCIs between January 2004 and January 2014. In the second part we will compare two different treatment regimens of PU through a randomized controlled pilot trial (RCT) where we will compare outpatient SCI follow-up in a hospital versus outpatient follow-up from the patient’s home, using telemedicine (teleSCI) interventions. We will compare the healing of the PU in the two groups (usual care versus teleSCI). The Tissue, Infection, Moisture Edge (TIME) registration form, the Photographic Wound Assessment Tool (PWAT) and the change in the ulcer size will be used to monitor the healing. Changes in health-related quality of life (HRQoL) and the need for assistance will be assessed using the Five Dimensions European Quality of Life scale (EQ-5D), the generic Medical Outcomes Study 12-item Short Form Health Survey (SF-12) modified version, the International Spinal Cord Injury Quality of Life Data set (ISCI-QoL Data set), and the Spinal Cord Independence Measure scale, version III (SCIM III). In addition to primary outcome measures, a cost-benefit evaluation and an assessment of patient satisfaction and participation will be performed, using customized questionnaires.

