### Sample size

For the demonstration of effect between the two groups, sample size calculation is based on an expectation of a standardized difference of at least 0.8 (typically considered a large effect). With 80% power, we will need 25 participants in each of the two groups hence we include 30 in each group to tolerate some drop outs.

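### Up to eight measures stand as primary with no rank or success rule, while the 80% power covers one continuous comparison on an unnamed outcome

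*Protocol article*

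**What the plan says.** The Primary endpoints section for study 2 opens with the effect of teleSCI "measured in terms of percentage wound size healed, and the time to heal". Under the same heading it then brings in:

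- TIME and PWAT, as tools for a systematic evaluation of the ulcer whose features are to be described.
- SF-12v, EQ-5D and ISCI-QoL: "Changes in self-reported health-related quality of life (HRQoL) and the need for assistance will be compared using the 12-item Short Form Health Survey" and the other two instruments. All three "will be used as a quantitative measure of the health outcome that reflects the participant’s own health judgment".
- SCIM III, for which "the results from both groups in the RCT will be compared with focus on changes in performing ability during the follow-up period".

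Time to heal has two definitions: "Time to heal will be measured counting days until healing, or measuring the amount of healing at the end of the 12-month follow-up period". The second overlaps with percentage wound size healed.

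The Secondary endpoints section begins only after this and covers services, satisfaction, participation and cost. The abstract has the same order. It lists the wound and quality-of-life instruments and then continues: "In addition to primary outcome measures, a cost-benefit evaluation and an assessment of patient satisfaction and participation will be performed".

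In the Sample size section, the "sample size calculation is based on an expectation of a standardized difference of at least 0.8", with 80% power and 25 per group, raised to 30 for drop-outs. No outcome is named. The Statistical analysis section gives chi-square and t tests for end-of-study data, regression to adjust for baseline differences, and mixed models for change over time. For quality-of-life scores and for percentage reduction in ulcer size it names both t tests and mixed models. The article states no significance level, no ranking of endpoints and no multiplicity rule.

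**The concern.** A primary endpoint fixes in advance which result decides the trial. Here the heading covers several measures, and nothing says whether success means any of them, all of them, or some order. For two groups of measures there are also two named analyses and no statement of which one counts. Under this text, a nominally significant difference on any one measure could be reported as a primary result.

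The power statement does not narrow this down. It describes one comparison of means, and the reader cannot tell which measure it was meant for. It does not describe time to healing with follow-up ending at 12 months.

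What is at stake is whether a positive finding can be read as confirming the stated hypothesis that healing is better with teleSCI, or only as one nominal result among several.

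**Working it through.** **Inputs from the protocol.** Standardized difference 0.8, power 80%, 25 evaluable and 30 randomized per group, 1:1 allocation (Sample size; Participants, Study 2). The measures are those under Primary endpoints. **Assumed:** two-sided 5% per test with no adjustment, because neither is stated.

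**1. Reproduce the stated sample size.** n per group = 2(z₀.₉₇₅ + z₀.₈₀)² / d² = 2(1.960 + 0.842)² / 0.64 = 24.5, so 25. This matches. The t-distribution version gives 25.5, so 26. A one-sided 5% test gives 20 and does not match, so two-sided 5% is the likely basis. Power at 25 per group is 79% (t) or 81% (normal). The step from 25 to 30 implies a drop-out allowance of 1 − 25/30 = 16.7%. The figure is correct for one continuous comparison.

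**2. Count the primary measures.**

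- Eight: percentage healed, time to heal, TIME, PWAT, SF-12v, EQ-5D, ISCI-QoL, SCIM III.
- Six: TIME and PWAT left out as descriptive.
- Two: only the measures in the opening sentence.

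**3. Chance of at least one false positive.** For k independent tests this is 1 − 0.95ᵏ. The correlated values come from simulation with equal pairwise correlation; the correlations are assumed.

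| Measures | Independent | r = 0.3 | r = 0.5 | r = 0.7 | r = 0.9 |
|---|---|---|---|---|---|
| 2 | 9.75% | 9.5% | 9.0% | 8.4% | 7.0% |
| 6 | 26.5% | 24.0% | 20.7% | 16.4% | 10.8% |
| 8 | 33.7% | 29.9% | 24.9% | 19.1% | 11.9% |

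**4. Two analyses of the same outcome.** If either a t test or a mixed model could carry the claim, 5% becomes about 6.4%, 7.1%, 7.8% or 8.3% when the two test statistics correlate at 0.95, 0.9, 0.8 or 0.7 (assumed). This adds much less than the number of endpoints does.

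**5. Power if the error rate were controlled by Bonferroni, d = 0.8.**

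| Measures | Level per test | Power at 25 per group (t) | Evaluable per group for 80% (normal / t) |
|---|---|---|---|
| 1 | 0.05 | 79% | 25 / 26 |
| 2 | 0.025 | 70% | 30 / 31 |
| 6 | 0.00833 | 53% | 38 / 40 |
| 8 | 0.00625 | 49% | 40 / 42 |

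For eight measures, 42 evaluable at the protocol's own allowance means 42 / (25/30) = 50.4, so 51 randomized per group.

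**6. Time to heal, illustration only.** By the Schoenfeld formula, the detectable hazard ratio at 80% power is exp(2 × 2.802 / √events). With an assumed 30 healed ulcers it is exp(5.603 / 5.477) = 2.78; with an assumed 40 it is exp(5.603 / 6.325) = 2.43. The protocol gives no healing rate, so neither count can be checked.

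**The case against.** The strongest defence has four parts.

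- **The trial is called a pilot** and follows the CONSORT extension for pilot and feasibility trials, so its results could be read as exploratory. This has some weight. However, the Sample size section aims to demonstrate an effect, the Hypotheses section predicts better healing with teleSCI, and the Objectives expect the results to influence guidelines. The label does not settle which measure decides.
- **The opening sentence may be the real primary pair**, with the rest as supporting instruments. That is a reasonable reading, and it is why the two-measure row is shown. Even so, the two are not ranked, and the quality-of-life and SCIM III comparisons stand under the same heading.
- **Alpha and multiplicity may be set in an analysis plan that is not shown.** This is correct, and their absence here is not in itself a fault. Such a plan would not change a protocol heading that covers eight measures, or a power sentence with no outcome.
- **The power statement is not empty.** One t test on percentage reduction with 25 per group is what it describes. This stands.

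A reader might infer that every primary measure is to be tested more than once. The text says so explicitly only for quality-of-life scores and percentage reduction. For SCIM III and time to heal it follows at most from the general analysis sentences, and no between-group test is given for TIME or PWAT. A reader might also infer a plan to test without adjustment, but silence does not establish that.

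**Conclusion.** The point holds as a defect in the protocol's own text: several unranked primary measures, no success rule, two named analyses without a deciding one for quality of life and ulcer reduction, and a power calculation tied to no outcome. At an assumed two-sided 5% per test without adjustment, the false-positive risk is 9.75%, 26.5% or 33.7% for two, six or eight independent tests. For eight, it falls to about 30% at pairwise correlation 0.3 and about 12% at 0.9. Every count and every correlation examined exceeds 5%.

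The consequence is that a single nominally significant result could not be taken as confirmatory. It would go too far to call a positive result uninterpretable: the inflation can be quantified, and results could be read after adjustment or as exploratory. The sample size arithmetic is sound for one continuous outcome. What is missing is the name of that outcome.

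**What to change.** - **Primary:** name one endpoint and one deciding analysis. Percentage reduction in ulcer size at the end of follow-up, with a healed ulcer counted as 100%, is the protocol's own measure and fits the 0.8 SD calculation. State whether the t test or the mixed model decides; the other becomes a sensitivity analysis.
- **Sample size:** tie the power sentence to that endpoint and state the two-sided 5% level. The 25 per group and about 80% power then stand.
- **Key secondary:** time to heal, defined only as days to complete healing and censored at 12 months, tested only if the primary is significant. Label any detectable hazard ratio as resting on an assumed number of healed ulcers.
- **Other secondary:** report TIME, PWAT, SF-12v, EQ-5D, ISCI-QoL and SCIM III with confidence intervals and no confirmatory claim.

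If the sponsor prefers several primaries, it should state a multiplicity rule and re-size the trial. Under Bonferroni with the t test, that means 31, 40 or 42 evaluable per group for two, six or eight measures.

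The recommended change is wording in three sections plus a matching registry update. It needs no new patients or data. The costs are that fewer results may be called primary, and that the choice comes late. The Trial status section reports about 50 participants randomized, nearly 40% of them finished, and data entry planned for autumn 2018. The choice must therefore be dated and documented as made before outcome data by group are examined. If that can no longer be shown, the report should say so.

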##### Secondary endpoints

The health care services as well as patient satisfaction and participation in both groups will be measured and evaluated using customized questionnaires.

In the cost-benefit form we will ask for time used at each consultation, travel distance to drive to and from the outpatient clinic at the SCI departments, as well as time used to travel, and distance driven for the local caregivers to and from the participants’ home. The number of caregivers participating in each session will be recorded, together with the total number of consultations for each participant, including teleSCI consultations, outpatient appointments at the hospital and telephone calls. Loss of working time for the participant and for any caregivers will be recorded, and so will medication and bandages used in every treatment session, both at the hospital and at home. CO_2_ emissions and costs for the environment will be mapped at every session.

Any technical problems will be mapped at every session. A custom-made questionnaire about the user’s experience with the follow-up will be mapped at the end of the follow-up period. This form contains questions about sufficient information provided before the inclusion, and during the follow-up period, as well as the participants’ experience regarding the follow-up. The results from the two groups will be compared with focus on differences in the user participation and satisfaction.

The investigators at the SCI departments at Haukeland University Hospital and Sunnaas Rehabilitation Hospital will supervise the filling in of the questionnaires and forms. After the conclusion of the follow-up period, a sample of participants will be requested to participate in a semi-structured qualitative interview based on the participants’ observation and experience.

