### Hypotheses

Epidemiological knowledge of persons with SCI and PUs will provide insight of this complicationCompared to other methods, PU treatment and healing will be more optimal by using teleSCI for follow-up at home measured in terms of healing, user interaction, and satisfaction

TeleSCI allows specialized hospital-based interdisciplinary teams to offer safe and effective treatment at home for persons with SCI and PUteleSCI enables specialized interdisciplinary health care workers to interact with, and empower, the primary health care workersOutpatient follow-up via teleSCI will shorten the time used for medical consultations when assessing PUOutpatient treatment via teleSCI will save money and time, compared with traditional treatment in hospital

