### Feasibility

The investigators conducted a feasibility study to explore the PU management by teleSCI before the current research project [11]. Wound healing, satisfaction, cost-benefit, and feasibility were mapped through logs, questionnaires, and semi-structured interviews with seven participants and their local caregivers. The results were promising, indicating that teleSCI is an acceptable and safe way to offer follow-up with regards to the technical solutions. Validated forms mapping QoL and function were used [21–23], as well as custom-made forms to map costs and participant satisfaction. Based on feed-back from the participants in the feasibility study [11], the forms have been improved to suit the current project.

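### Investigators at the departments that deliver the follow-up supervise the form on which unblinded participants rate that follow-up, so courtesy answers may differ between arms

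*Protocol article*

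**What the plan says.** Under Secondary endpoints, the article describes a custom-made questionnaire given at the end of follow-up. It covers the information participants received and their experience of the follow-up, and the arms are to be compared on participation and satisfaction. The section then states that the investigators at the SCI departments of the two trial hospitals "will supervise the filling in of the questionnaires and forms". No form is excepted.

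Under Blinding: "In study 2, it will not be possible to blind the participants". The wound assessment tool and the cost-benefit form "will, however, be considered by blinded medical professionals not participating in the research project". No other form is given this protection. The section adds: "Only the randomized number, not the identity of the participants, will be known during the analyzing part of study 2".

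Under Randomization and allocation concealment: "At least two persons, either investigators or other medical staff members, will be present to secure the allocation procedure".

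Under Hypotheses, teleSCI is expected to do better, "measured in terms of healing, user interaction, and satisfaction".

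**The concern.** The wound teams of the two SCI departments deliver the follow-up in both arms. If investigators from those departments oversee the form that rates this follow-up, a participant may answer more kindly than in private. Courtesy that is equal in both arms would cancel in the comparison. It need not be equal here, because the teleSCI arm meets the team on a schedule and the usual care arm meets it on request.

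At stake is the satisfaction and participation comparison, a secondary endpoint that is also one of the yardsticks in the hypothesis on teleSCI. A difference on it could mix the participant's view of teleSCI with regard for the team. Unblinded participants cannot be avoided in this trial, but supervision by the provider's own department can.

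**Working it through.** **1. Who supervises, and who is masked**

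| Point | Article section | What it gives |
|---|---|---|
| Supervisor of forms | Secondary endpoints | Investigators at the two SCI departments |
| Provider of follow-up | Participants, Study 2 | Wound teams of the same departments, both arms |
| Participant | Blinding | Not blinded |
| Blinded assessment | Blinding | Wound tool and cost-benefit form only |
| Investigators at allocation | Randomization and allocation concealment | May be present; no section masks them |
| Masking at analysis | Blinding | Hides identity, not the arm at the time the form is filled in |
| Baseline | Randomization and allocation concealment | Before randomization, so only end-of-follow-up forms are exposed |

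**2. Contact with the team**

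The teleSCI arm is seen at intervals of two to three weeks for at most 52 weeks. If the ulcer does not heal, that is 52/3 ≈ 17 to 52/2 = 26 scheduled contacts. Usual care has no schedule (The usual care group).

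**3. The plan's own figure**

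The Sample size section gives 25 per group for a standardized difference of 0.8 with 80% power. It does not state alpha; two-sided 5% is assumed here.

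n = 2 × (1.960 + 0.842)² / 0.8² = 2 × 7.85 / 0.64 ≈ 24.5, so 25 per group.

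The figure reproduces (the exact t calculation gives 25.5, so 26). The point does not depend on it, but it fixes the planning range of 25 to 30 per arm.

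**4. Illustration of a differential shift**

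Assume no true difference and a shift of b SD between arms from reporting alone. The value of b is an assumption.

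Standard error of the standardized difference with n per arm = √(2/n). For n = 30 it is √(2/30) = 0.258. The noncentrality of the t test is b × √(n/2); for b = 0.3 and n = 30 it is 0.3 × √15 = 1.16.

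Probability that the two-sided 5% t test rejects:

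| b (SD) | 30 per arm | 25 per arm |
|---|---|---|
| 0 | 5.0% | 5.0% |
| 0.1 | 6.7% | 6.4% |
| 0.2 | 11.9% | 10.7% |
| 0.3 | 20.8% | 18.0% |
| 0.4 | 33.2% | 28.3% |
| 0.5 | 47.8% | 41.0% |

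The test is symmetric, so the same rates apply if the shift runs against teleSCI.

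**5. How many forms can still change**

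Trial status reports about 50 randomized, with nearly 40% of them finished: 0.4 × 50 = 20. Of the planned 60, about 60 − 20 = 40 end-of-follow-up forms were still to come when the article was written.

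**The case against.** **Supervision may be administrative.** It can mean checking that forms are complete, and no section says that the supervising investigators are the treating clinicians. This stands as a limit. If it is the intended meaning, the sentence should say so, and the same small change settles it.

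**Both arms are treated alike.** The sentence applies to both, and greater satisfaction from frequent contact may be a real effect of teleSCI. This also stands: a differential shift is possible, not shown. A supervised form cannot separate the two explanations.

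**Quality of life.** A reader might infer that SF-12, EQ-5D and ISCI-QoL are compromised to the same degree. The article does not support that. These measures are described under Primary endpoints, and only the general wording of the supervision sentence reaches them. They rate the participant's own health, so courtesy towards a provider fits them poorly.

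**The investigators' stake.** A reader might infer that the investigators developed teleSCI. The article says only: "The investigators conducted a feasibility study to explore the PU management by teleSCI before the current research project". The technical solution is attributed to an existing telerehabilitation model.

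**The numbers.** The shift is assumed, and at 0.1 SD the error rate is close to nominal. Participants also remain unblinded after the change, so it removes only the part that is due to supervision.

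**Posting carries its own risk.** About 50% had answered the Study 1 questionnaires when the article was written. Trial participants may respond better, but postal return should not be the only route.

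**Conclusion.** The point holds, mainly for the end-of-follow-up experience, satisfaction and participation form. The article states a procedure that places provider-side investigators over the form rating their own department's follow-up, and its blinding provisions do not cover that form. That the investigators know the allocation is an inference from the Blinding and Randomization sections; the article does not say so directly.

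A reader might infer that the comparison is biased towards teleSCI by a known amount. The documents give neither size nor direction. The range of about 7% to 48% rests wholly on an assumed shift of 0.1 to 0.5 SD, 30 per arm and no true difference; with 25 per arm it is about 6% to 41%.

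Percentage wound healing and time to heal do not depend on this form and are not affected.

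**What to change.** Change the supervision sentence under Secondary endpoints as follows.

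- The participant completes the end-of-follow-up satisfaction and participation form in private. Where hand function requires help, a relative or existing staff member who is not on the wound team gives it.
- The form goes into a sealed envelope marked only with the project number. It is handed in at the final assessment, or posted with a reminder, and opened at data entry.
- The self-reported quality-of-life forms follow the same route as a secondary precaution.
- Investigator supervision is limited to clinician-completed forms and to checking that the other forms were returned.
- Forms already completed under supervision are recorded as such. The satisfaction comparison is reported with and without them as a descriptive sensitivity analysis; with about 20 such forms it cannot test for an effect of the mode of completion.

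The cost is a procedural amendment, envelopes and some postage, with no extra staff. Somewhat more missing items should be expected, and handing in at the final assessment limits this. The mode of completion will be mixed, because nearly 40% of about 50 randomized participants had already finished.
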